**Introduction to the survey: data protection and technical instructions**
Information on data protection regulationsInformation on responding via tablet and computer or laptop (exclusion: smartphone or iPhone)Information sheet for participants (PDF download)Declaration of consent for participants (as PDF download)Obtaining consentInstructions on how to respond to the survey, introduction to question formats, and options for saving an intermediate response status
**Testing of cognitive abilities and perception**
A total of 5 picture and text questions (picture recognition, object naming or assignment, temporal or spatial orientation, and memory)Identification of cognitive and perceptual limitations with possible influence on the questionnaire responseBasis: standardized assessments for identification of aphasia, apraxia, visual or perceptual deficits, and cognitive deficits
**Introduction to the survey: background of the digital stroke rehabilitation**
Information about the diagnosis of stroke (incidence and shortage of specialists)Information about digital technologies (ie, digital support systems) in therapiesIntroduction of terms (digital support systems and digital therapies)Information about patient and public preferences, survey content (preference information, experiences, expectations, attitudes, and sociodemographic data), and survey process and structure
**Inclusion and representativeness of the study population**
Inclusion: age <17 years, German language skills=intermediate to very good, and, only for experimental group, diagnosis of stroke=is presentRepresentativeness in control group based on quota in age, sex, education, and state (for state, not present as quota in sampling)
**Diagnosis-related questions**
Objective: to separate the study populations into patients with stroke and the general populationDiagnosis of stroke; time of diagnosis; consequences of stroke related to physical functions, daily life, and support needs; and current treatment needs
**Introduction to the preference survey**
Description of the scenario: rehabilitative therapy using digital technologyDescription and explanation of digital therapies (wording: digital support systems)General definition and delimitation of the terms attributes and attribute levelDescription and illustration of all 7 attributes and attribute expressionsExample or tutorial for answering a choice set
**Preference elicitation or discrete choice experiment**
Dominance test: selection from a choice set with an openly dominant alternative (no copayment and 100% treatment success) to test the understanding of choice tasks and quality (validity)6 Choice tasks: choice best, choice second best, and dual response
**Additional questions**
Evaluation of therapy goals as activities in daily life via a 5-point Likert scaleAssessment of digital transformation goals in terms of flexibility of place, time, performance, and adaptability via rankingSociodemographic questions (expanded) on marital status, household or residential situation, and occupational statusHealth status and quality of lifeRehabilitative therapy experiencesExperiences with and attitudes toward digital technologies for one’s own healthQuestionnaire assessment to evaluate the quality of the surveyQuestions on digital health literacy
**Completion of the survey**
AcknowledgmentInformation on how to contact the study team and collaborators

### Statistical Analyses

Discrete choice models differ from regular logistic regression because the data are grouped. These models consider the structure of the DCE data, with the same participant providing multiple results for a sequence of different election scenarios [59].

We analyzed the results using conditional logistic and mixed logistic models and performed a latent class analysis to identify heterogeneous preferences [60]. We used the conditional logistic model to calculate the coefficients whose signs indicated a preference direction. Positive coefficients indicated a positive influence of a trait expression, and negative coefficients indicated a negative influence. The larger the coefficient, the greater the influence on the choice decision. The distances between 2 property expressions indicated the magnitude of the influence. The assumption of normal distribution in the conditional logistic model limited the informative value of the calculated coefficients. We used mixed logistic models to analyze preference differences as a function of each individual by calculating SDs and SEs. We tested assumptions to determine whether the preferences of specific groups differed from each other in terms of characteristics, experiences, and cultural background. Latent class analysis was used to generate information on the heterogeneous groups. We used StataCorp LLC to conduct our statistical analyses.

For our analysis, the results from both groups were compared. We did not directly compare the coefficients because of scale effects [61]. The comparison was made by considering the influence of the covariate general population.

### Study Sample

We include study participants depending on the target population, sample selection, and the qualitative or quantitative study part of the survey. The quantitative pilot interviews were conducted between March and September 2020. The qualitative pretest interviews were conducted between October and December 2021. The quantitative survey was started by pilot testing (n=150) in January 2022. After pilot testing, participants of the general population will be recruited via a panel provider and patients with stroke will be recruited via a panel provider, E-BRAiN clinical study and Stiftung Deutsche Schlaganfall-Hilfe, and from social networks. The study sample is based on a nonprobability ad hoc sample selection as a self-selection sample depending on availability and on a nonprobability ad hoc sample selection as a quota sample [62,63]. Regarding the full E-BRAiN project, recruitment and in-person participation of patients with stroke were planned within the clinical project. The DCE project was planned in relation to the clinical recruitment and was adjusted according to the pandemic-related constraints and financial resources. Therefore, panel recruitment was expanded to include patients with stroke in the DCE project.

### Data Collection

Calculating the sample size for the choice experiments is complex [64]. The question format, complexity of the choice task, desired precision of the results, and need for subgroup analysis are criteria that could modify the sample size [29,65].

For a robust quantitative evaluation of the main effects of a DCE in a simple logistic regression model (eg, mixed logit regression model or conditional logistic model), we calculated the sample size using the following formula: *(n*
*× t × a) / c ≥1000; n = (1000 × c) / t × a*, where *n*=number of participants, *t*=number of choices (choice sets), *a*=number of choice alternatives per choice set, and *c*=number of levels (for main effects, *c*=number of levels of the attribute with the highest number of levels and for interaction effects, *c*=the largest product of the levels of the 2 attributes with the highest number of levels).

Given 6 choice tasks and 3 alternatives described by attributes with a maximum of 5 levels, a minimum number of 300 participants (*n = [1000 × 5] / [6 × 3]*) is needed to represent at least the main effects approximately 1000 times. This resulted in a target sample size of 300. When considering the interaction effects (*c*=15 in the formula), the resulting *n* is at least 1000 (*n = [1000 × 15] / [6 × 3]*). To adequately account for interaction effects, a sample size of at least 1000 is required to ensure sufficient representation. The final target sample size is approximately 1000 participants.

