### Elicitation Tasks

The challenge in a DCE is to dissolve the response uncertainty and to trace the preference information back to the individual attributes through repeated choice tasks, with participants “forced” to make a decision between digital therapies. For the professional group, there was no choice available within the choice task. The underlying choice task is a ranking task, which follows a fixed procedure. The choice starts with the selection of the best alternative among 3 choices. The choice is iterated with the remaining 2 so that a complete ranking is achieved. Thus, the DCE uses a best-best choice format [51].

Participants’ willingness to choose the digital therapy was determined by the following follow-up question: “Would you really choose the previously selected digital therapy in real life to improve your health?” Recently, the dual response “none” has been established as a variant in choice experiments [52,53]. A dual response of “none” asks for 2 responses for each task: one choice between the available product alternatives and one between the “none” concept and the previous alternatives. Essentially, it is a choice between the most preferred alternative and none. If participants would actually buy or take the alternative, they would not prefer none, but if they would not buy or take the alternative, they would prefer none to the given alternative [54]. The dual response “none” design takes more time to answer and is an increase in analysis effort owing to a complex design. However, more information is generated, which makes the design more efficient and powerful. Estimation errors are reduced, and the underlying model estimate is not significantly changed [52]. This design provides a higher resolution for individual-level preferences. As there is less “missing” information when participants select “none” as their preferred alternative, more information is available for individual-level modeling [54]. The final survey instrument comprised 6 choice tasks. The number of choice tasks was determined by the underlying experimental design, possible number of participants, and information received per task. No names, brands, or companies were named in the presentation of the choice tasks; therefore, the tasks were unlabeled. In addition, unlabeled alternatives were preferred because the study objectives were to estimate the marginal rates of substitution and value equivalents for therapy attributes [18].

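### The interaction sample size uses c = 15 where the plan's own definition gives c = 25 (n = 1389, not 1000), so 15 of the 21 attribute pairs miss the plan's threshold at the target of about 1000

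*Protocol article*

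**What the plan says.** All of the sizing is in Data Collection. The rule is printed as "t × a) / c ≥1000; n = (1000 × c) / t × a", where t is the number of choice sets, a the number of alternatives per set and c a level count. For main effects, c is the level count of the attribute with the most levels. For interactions the definition is "c*=the largest product of the levels of the 2 attributes with the highest number of levels".

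The inputs are given as "Given 6 choice tasks and 3 alternatives described by attributes with a maximum of 5 levels". Elicitation Tasks agrees on both: "The final survey instrument comprised 6 choice tasks" and "The choice starts with the selection of the best alternative among 3 choices". The main-effects result is given as 300.

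For interactions the article puts c at 15 and writes "the resulting *n* is at least 1000 (*n = [1000 × 15] / [6 × 3"]. It then says that at least 1000 participants are required for interactions to be sufficiently represented, and concludes: "The final target sample size is approximately 1000 participants".

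Two other places bear on this. Experimental Design says that main and interaction effects will both be analysed, and that each choice task shows 4 of the 7 attributes. Table 1 gives the level counts, and its footnote confirms that contact with professionals has 3 levels, data processing has 4, and the range is 3 to 5.

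**The concern.** The definition of c, the value used for c and the result of the division are all printed within one section, and they do not agree. The definition takes the two attributes with the most levels. The value 15 can come from Table 1 only as 5 x 3, which brings in the attribute with the fewest levels. In addition, the division shown does not give 1000.

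The final target is set by this line, and this rule is the only sample-size justification in the article. A reader would conclude that every two-way interaction between attributes meets the plan's own standard of 1000 representations. What is at stake is that adequacy claim for an analysis the article says it will carry out.

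**Working it through.** **Inputs**
- t = 6 and a = 3, so t x a = 18 (Data Collection; confirmed in Elicitation Tasks).
- Threshold: 1000 representations (Data Collection).
- Level counts from Table 1: explanation 5, information 5, patients' choice 5, copayment 5, therapy success 5, data processing 4, contact 3.
- Partial design: 4 of 7 attributes per task (Experimental Design).

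**Formula.** n = 1000c / (t x a). The general formula is printed without brackets around t x a, but the worked examples bracket 6 x 3, so that reading is used. A literal left-to-right reading would give 1000 x 15 / 6 x 3 = 7500, which is plainly not intended.

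**The plan's own figures**
- Main effects, c = 5: 5000/18 = 277.8, so 278. The stated 300 is a round-up and meets the rule (300 x 18/5 = 1080).
- Interactions as printed, c = 15: 15000/18 = 833.3, so 834. The stated 1000 is not reproduced. With t x a = 18, n = 1000 needs c = 18, which is not a product of two level counts in Table 1. With c = 15, n = 1000 would need t = 5, but the article fixes t at 6.

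**The rule applied as defined.** The two largest level counts are 5 and 5, so c = 25 and n = 25000/18 = 1388.9, so 1389. The target of 1000 is 389 short, 28% below 1389.

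**Representation at n = 1000, formula as written (18000/c)**

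| Pair type | Number of pairs | c | n needed | Representations at n = 1000 |
|---|---|---|---|---|
| 5 x 5 | 10 | 25 | 1389 | 720 |
| 4 x 5 | 5 | 20 | 1112 | 900 |
| 3 x 5 | 5 | 15 | 834 | 1200 |
| 3 x 4 | 1 | 12 | 667 | 1500 |

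The pairs total 10 + 5 + 5 + 1 = 21. Fifteen miss the threshold. The six that meet it all involve the contact attribute.

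**Allowing for the partial design.** The formula treats every attribute as present in every task. Assuming the attributes appear equally often, a given pair is shown together in (4 x 3)/(7 x 6) = 2/7 of tasks. Multiplying the last column by 2/7 gives about 206, 257, 343 and 429 for 5x5, 4x5, 3x5 and 3x4 pairs. On that count no pair reaches 1000.

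**Main effects at the target.** The formula as written gives 1000 x 18/5 = 3600 representations for a 5-level attribute. With a 4/7 share of tasks this is about 2057, still above 1000.

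**The case against.** Four points can be made for the plan.

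*1000 is a cautious round-up of 833.* This is fair for the division alone. The main-effects figure is also rounded up, from 278 to 300, and a larger n does no harm. But the article presents 1000 as what the expression gives, with no rounding or dropout allowance stated, and rounding does not repair c.

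*The rule is a heuristic.* It has no alpha, power or effect size, so 720 instead of 1000 is not a demonstrated loss of power. That stands. The article nevertheless uses the rule to claim adequacy, and on its own definition the claim fails.

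*The ranking task yields more information per set.* Each task also collects a second-best choice. Counting these as further sets (t = 12) would give 25000/36 = 694 for c = 25. But the article defines t as the number of choice sets, uses 6, and claims no such credit.

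*No stated objective depends on an interaction.* This also stands. A reader might infer that the shortfall undermines the benefit-burden objective, for example through a success by copayment interaction. The documents do not support that. The objective is to estimate the maximum acceptable burden, and Elicitation Tasks speaks of marginal rates of substitution, which main-effect coefficients can supply. No objective or hypothesis names an interaction between two attributes. Interactions enter through a general statement in Experimental Design and through the sample-size line.

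**Conclusion.** The inconsistency is real, and nothing elsewhere in the article reconciles it. As defined, c is 25 and the rule asks for 1389 participants. The article uses 15 and reports 1000. At 1000 participants, 15 of 21 attribute pairs fall short of the plan's threshold on the formula as written, the ten 5x5 pairs by 28% and the five 4x5 pairs by 10%. The 833-versus-1000 slip is secondary because it errs on the safe side.

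These results rest only on Table 1 and the printed rule. The partial-design figures (about 206 to 429) rest on the further assumption that attributes appear equally often.

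A reader might infer that the study is too small overall or must recruit 1389. That does not follow: the main-effects requirement of 278 is untouched by this error and the target exceeds it comfortably. A reader might also infer that only pairs of a 3-level with a 5-level attribute meet the rule. The single 3x4 pair, contact with data processing, meets it too. What fails is a stated sample-size figure and the claim about interactions built on it.

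**What to change.** In Data Collection:

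1. Set c for interactions to 25 and give n = 1389. If c = 15 is kept as an illustration, give n = 834 and say that it applies to pairs of a 5-level attribute with the contact attribute.
2. Keep the target of about 1000 and withdraw the statement that 1000 ensures sufficient representation of interaction effects.
3. State the representation achieved at 1000 participants with the partial design taken into account. Under equal appearance of attributes this is about 206, 257, 343 and 429 for 5x5, 4x5, 3x5 and 3x4 pairs. The counts from the actual design should replace these if they differ. The unadjusted 720 to 1500 should not stand alone, because they overstate what participants see.
4. Label all two-way interaction results as exploratory.

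Coding copayment and therapy success linearly would reduce the number of interaction terms. That is an optional modelling choice and not part of this correction.

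The cost is wording only. The stated figure becomes less favourable, and no extra participants are needed.

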### Data Quality

Our data quality criteria are as follows. First, we require data security. The web-based survey is developed and scripted by the research team. Quality assurances are also conducted. The quality tests follow a predefined test grid. Second, we ensure data integrity by conducting several quality assurance steps, including extensive end-to-end testing, data export and tabulation of test data before the live sample will be launched, validation of the experimental design scripts, and validation of the data analysis scripts. Third, our data require validity and reliability. The following indicators of validity and reliability are collected: completion of the entire web survey in a short period, selection of the predominant alternative in the fixed-choice question, selection of a different alternative in the repeat question, selection of “best” and “second-best” levels always based on a single attribute, straightlining (ie, always the same answer choice in each choice set), and additional questions to verify DCE data and class determination.

## Results

The literature review, qualitative preliminary study, survey development, and pretesting were completed. Recruitment of the experimental group and the control group started in January 2022. Recruitment of the experimental group (patients with stroke) will be conducted in conjunction with the clinical trial of the collaborative project E-BRAiN. All patients in the clinical trial will be surveyed. Data collection and analysis will be completed in the last quarter of 2023.

## Discussion

### Principal Findings

Acceptance is a multidimensional construct. The requirements for digital technologies include various dimensions [66]. Digital technologies in postacute rehabilitative therapies are increasingly used for patients classified as cognitively, perceptually, and participatively impaired. [67]. These technologies are still largely unknown to users. Successful implementation depends on the acceptance of the patients [18]. In addition to expected clinical success, technical features also affect consumer acceptance.

This paper describes the development of a HPR study. Patient preference information will be provided by analyzing 7 attributes in a DCE. With respect to the mantra of HPR that “choice defines value,” the study objective is to weight criteria that impact patient acceptance. Furthermore, a benefit-burden assessment, an overall comparison of different alternative digital interventions, interpretation of adherence, analysis of heterogeneity, and subgroup analysis are aimed at improving decision-making for innovative interventions, such as adopting new digital technologies such as artificial intelligence (AI). This study includes several aspects that further test the hypotheses related to needs, outcomes, technical aspects, human contact, goals of digital transformation, and personal information about patients.

To achieve the objectives, formative preliminary studies were conducted. A list of 17 attributes was tested. The final list of attributes represents the decision context of digital transformation in health care: explanation and presentation of therapy exercises, information in therapy, contact with health professionals, and data processing. To complete the decision context, copayment per month and therapy success within 6 months were added.

To develop the final survey instruments, attributes were described and visualizations for each level were added in a descriptive framework. The developed fractional-factorial efficient Bayesian (D-error) experimental design includes a best-best ranking task in a partial profile. A web-based questionnaire was developed by integrating additional questions on patients’ characteristics, experiences, and cultural background. Pretest interviews and pilot testing have led to the holistic adaptation of the survey instrument in terms of descriptions, visualizations, and questions to enhance patient understanding as well as the testing of the experimental design. The analysis, with the help of a conditional logit model, proved the assignment of substantially results and unambiguous β coefficients to the attributes and levels, thereby demonstrating the effectiveness of the experimental design. The further study will use mixed logit models and heterogeneity analysis to evaluate the final study results.

This study demonstrates the importance of investigating patient acceptance and the technical aspects of digital technologies such as AI. Dai and Tayur [68] highlighted in their research that the uniqueness bias is a barrier to patient acceptance, as patients attribute more individuality to a human-guided therapy than to an AI-based solution. To solve this bias, a study of patient perceptions and preferences is recommended [68]. Furthermore, research on rhetoric to improve the adoption of digital technologies such as AI shows the importance of communicative strategies [69]. Another aspect that influences patient acceptance is data privacy and security and the associated risk [70].

To the best of our knowledge, this HPR study conducted a DCE. We attempt to develop a generic model that generates preference information to provide information on patient acceptance of digital technologies.

### Limitations

Further investigation must consider the following limitations and challenges:

Digital transformation in health care is characterized by a large number of attributes to achieve goals (eg, flexibility). The development of the underlying descriptive framework was difficult. Therefore, we consider the goal of digital transformation.The characteristics of the experimental group lead to different challenges. Patients with stroke often have limitations related to their cognition, perception, and movement (motor function). This leads, on the one hand, to recruitment challenges owing to lower participation possibilities and lower response rate and, on the other hand, to challenges in the design, layout, and formulation of the questionnaire. Furthermore, pandemic-related inaccessibility was expected.Limited financial resources limit the additional number of patients with stroke that can be enrolled via a panel.Owing to the recruitment challenges, we decided to include a control group (the general population). Because of the scale effects, the coefficients will not be compared directly. The comparison will be made by considering the influence of the covariate general population.Analysis of preference differences between the experimental and control groups will be limited because financial resources do not allow adequate number of patients with stroke to be available via a panel survey.

Another limitation relates to the interpretation of the concept of “value.” The term “value” is a broad term used in different contexts. In general, “value” refers to the worth, importance, or usefulness assigned to something based on individual perceptions. However, “value” can be determined by a wide range of terms, such as personal beliefs, societal norms, economic considerations, and preferences. The economic perspective considers the exchangeable value of goods or services. In contrast, “value” can also compass moral, ethical, or philosophical principles that guide individuals’ behavior. Therefore, it is crucial to emphasize at this point that there is a potential limitation in this paper where the term “value” may be subject to misunderstanding. In this study, the concept of “value” is distinguished from “value judgments”. The term “value judgments” describes the context of ethical, moral, or philosophical aspects [71]. In the context of HPR, “value refers to the subjective assessment of the importance, desirability, or utility individuals assign to specific health-related outcomes or interventions.” It involves understanding and measuring the preferences of individuals when making decisions related to their health and health care. In contrast to judgments, preferences relate to individual choices that are based on subjective likes or dislikes. This is unclear as is. Do you mean “The guiding principle of HPR is encapsulated in the mantra “choice defines value.” This concept highlights the importance of gaining a deeper understanding of patients' preferences, enabling health care providers, regulators, and policy makers to better address the needs of patients? Please revise as applicable [72,73]. As preferences can be influenced by judgments, social determinants, environmental factors, or experiences, we included several questions in the final survey instrument that could be mapped to these influencing factors (eg, cultural background, experiences in therapy, experiences with digital health, and attitudes toward digitization). These questions can be consulted when analyzing the differences between patient groups.

